
### Data collection

Data will be collected before the intervention, during the intervention at week 3, 6 and 9, and directly after the 12-week intervention. Follow-up assessments will be at 6 and 12 months after the start of the intervention. One month after completion of the intervention, a consecutive sample from each of the two intervention groups (n = 15) will be interviewed regarding their experiences of the intervention and eventual benefits.

All online self-assessment scales will be completed digitally in the S-T electronic data capture platform. The data system will automatically send e-mails to participants informing them to log on to the portal to complete the questionnaires, and will notify them when an assessment is approaching or if a questionnaire has not been completed. Notifications will also be sent by e-mail if questionnaires are not completed within the set time frame. Participants who prefer paper questionnaires will have them sent by post together with an envelope with prepaid postage, and questionnaires will be stored in a locked facility at the University Health Care Research Centre at Örebro, to which only the research team will have access. Physical examinations and magnetic resonance imaging (MRI) examinations will be performed during visits to the outpatient clinic and X-ray clinic, respectively.

Data will be collected both in paper and digital formats and stored in locked fireproof cabinets when not being processed, or on a password-protected server within Region Örebro County (RÖL). The material collected will be provided with a code in place of personal data, and only authorized persons will have access to the code key and materials.

Only authorized project members will have access to all folders and subfolders. The principal investigator (MM) and data handlers will have authorization to read and write in the files under project documents, original data, and personal codes. Collected data will be stored in accordance with current legislation and local guidelines for at least 10 years after publication. All project data will be stored on the server, which can only be accessed at RÖL or via a virtual private network (VPN) or, outside RÖL’s area, with a password to the computer and VPN.

### Outcome measures

See Table 3 for a summary of measures given by time point.

**Table 3 Tab3:** Measures by time point

	Completed by:	Visit 1	3 weeks	6 weeks	9 weeks	12 weeks (end of the intervention)	6- month follow- up	12- month follow- up
Informed consent to trial participation	PT							
**Primary outcome measures (ADHD symptoms)**								
MADRS-S*	PT					P	P	P
WHO Adult ADHD Self-Report Scale (ASRS-v1.1)		P		P		P	P	P
Clinical Global Impression-Severity (CGI-S)	AP					AP	AP	AP
Clinical Global Impression- Improvement (CGI-I)						AP	AP	AP
**Secondary outcome measures**								
Patient-rated Global Impression-Improvement (PGI-I)				p		P	p	p
Quality of life (QoL) assessed with the EQ-5D-5 L*		p		p	P	P	p	p
Ekblom-Bak (EB) submaximal exercise test		PT				PT	PT	PT
Balance on one leg (60-second Flamingo balance test)		PT				PT	PT	PT
Grip strength		PT				PT	PT	PT
Body mass index (BMI)		PT				PT	PT	PT
Abdominal circumference		PT				PT	PT	PT
Body Awareness Scale -Movement Quality and Experience (BAS MQ-E)		PT				PT	PT	PT
Physical activity and steps measured using an accelerometer, 7 days		P				P	P	P
Swedish National Board of Health and Welfare’s indicator questions about exercise and training habits		P	P	P	P	P	P	P
**Mental function**								
Cognitive tests on computer (AX-CPT*, Go/NoGo, IAPS*)		AP				AP		
Magnetic resonance imaging (MRI) examination		AP				AP		
**Everyday function**								
The Canadian Occupational Performance Measure (COPM)		OT				OT	OT	OT
Assessment of Time Management Skills, Swedish version (ATMS-S)		P				P	P	P
Satisfaction with Daily Occupations-Occupational Balance (SDO-OB)		OT				OT	OT	OT
Adult ADHD Quality of Life Questionnaire (AAQol)		P				P	P	P
General Self-Efficacy 10-item Scale (GSES-10)		P		P		P	P	P
Self-efficacy for exercise (SEE-S)		P	P	P	P	P	P	P
Insomnia Severity Index (ISI)		P	P	P	P	P	P	P
Interviews						OT, PT		

ADHD = attention deficit hyperactivity disorder. AP = assistant psychologist; OT = occupational therapist; P = participant; PT = physiotherapist.

*For the names of instruments not appearing in full here, please see the Abbreviations list

### Primary outcome measures

Changes in ADHD symptoms:

The WHO Adult ADHD Self-Report Scale (ASRS-v1.1) [32]. The ASRS-v1.1 is a self-assessment form consisting of 18 questions corresponding to the 18 criteria for ADHD according to the Diagnostic and Statistical Manual of Mental Disorders, Text Revision, 4th edition (DSM-IV-TR). Part A consists of six questions that predict ADHD while part B consists of twelve questions about other symptoms. The ASRS-v1.1 has shown good reliability and validity [32].The Clinical Global Impression-Severity scale (CGI-S). The CGI-S is used for clinical assessment of the severity of symptoms [35]. The CGI–S scale reflects the patient’s total psychiatric impairment. It provides an overall clinician-determined summary measure that takes into account all available information, including knowledge of the person’s history, psychosocial circumstances, symptoms, and behaviour, and the impact of the symptoms on the person’s ability to function.The Clinical Global Impression-Improvement scale (CGI-I) [35]. This is a clinician-rated instrument which provides self-rated global measures of improvement and treatment satisfaction on a 7-point scale, from 1 = very much better to 7 = very much worse [36].

### Secondary outcome measures

Clinical variables:

The Patient-rated Global Impression-Improvement scale (PGI-I) [35].The EQ-5D-5 L [37, 38], developed by the EuroQol Group. The EQ-5D-5 L is a QoL measure for assessing an individual’s health status, using a 5-level scale ranging from “no problem” to “extreme problems”, divided into five dimensions of mobility, self-care, usual activities, pain/discomfort, and anxiety/depression. The EQ-5D-5 L can also be used to generate a utility value that ranges from 0 (dead) to 1 (perfect health). By multiplying the time spent in a given health state (baseline – 3 weeks – 6 weeks – 9 weeks – 6 months – 12 months) by the average utility weight associated with the period (using the trapezium rule), quality-adjusted life years (QALYs) will be derived. This will be used in the health economic evaluation.

Physical function:

The Ekblom-Bak (EB) submaximal exercise test. The EB test is a valid measure of maximal oxygen uptake (VO_2_max) for a wide variety of ages [39, 40].The Flamingo balance test is a 60-second one-leg stand test measuring static balance and stability in the abdominal, pelvic and leg muscles [41, 42].Grip strength measured with a hand-held dynamometer JAMAR, (Item 3363, G.E. Miller, Inc., [name]) a reliable and valid measure in healthy participants as well as across various clinical populations [43, 44], will be tested, and height, weight and waist circumference will be measured using standardized tests [45]. Thereafter, body mass index (BMI) will be calculated.The Body Awareness Scale-Movement Quality and Experience (BAS MQ-E) will be used for physiotherapeutic assessment of body awareness [46]. The psychometric properties of this scale have been reported to be good [47].An accelerometer (Actigraph GT3X+; ActiGraph, Pensacola, FL, USA) will be used to measure levels of daily physical activity and general health [48–51].The Swedish National Board of Health and Welfare’s indicator questions about exercise and training habits [52] will be used to assess physical function.

Cognitive function:

Computerized cognitive tests such as the AX-Continuous Performance Test (AX-CPT) and the Go/No-Go motor response inhibition test will be used to test mental function, and the International Affective Picture Series (IAPS) to test emotion regulation [53–55].An MRI examination with structural and functional brain imaging at rest (rest fMRI) and during brain activation, with cognitive (AX-CPT), motor (Go/NoGo) and affective (IAPS) paradigms [56–58], will be performed in 25 participants from each group.

Everyday functioning:

The COPM [33, 34], a person-centred instrument that, during an interview, identifies, validates and prioritizes difficulties that negatively affect the person’s performance of activities in daily life, forms the basis for setting occupational therapy intervention goals. The person identifies performance problems and rates them on a scale of 1–10, where 1 = unable to perform at all and 10 = able to perform extremely well. After that, up to five difficulties are prioritized that the intervention should be aimed at. In the case of pre- and post-measurement, performance and satisfaction can be assessed separately. The COPM has been used in people of different ages, diagnoses and backgrounds. Reliability and validity as well as sensitivity to change are good [33, 34].The Assessment of Time Management Skills, Swedish version (ATMS-S) [58], will be used to assess time management. The ATMS-S is a self-assessment form consisting of 27 items divided into three subscales: time management skills (eleven items), organization and planning (eleven items), and regulation of emotions in relation to time (five items). The ATMS-S has been reported to have good psychometric properties [59].The Satisfaction with Daily Occupations-Occupational Balance (SDO-OB) [57] scale. This interview instrument contains 13 items that measure a person’s activity level and satisfaction with their daily activities as well as their perceived activity balance in the areas of: work/study (three items), leisure (three items), housework (four items), and self-care chores (three items). The SDO-OB scale has been developed in Sweden for people with mental disorders and exhibits good psychometric properties regarding internal consistency, validity and test-retest reliability [57].The Adult ADHD Quality of Life questionnaire (AAQoL) [56]. This is a self-assessment form containing 29 items that measure everyday functioning and QoL in areas that research has shown to have an impact on ADHD specifically. The form has four subscales: life productivity (eleven items), psychological health (six items), QoL (seven items), and relationships (five items). The AAQoL has been shown to have good psychometric properties [56, 60].The General Self-Efficacy ten-item Scale (GSES-10) [61]. This is a self-assessment form with ten items that are scored on a 4-point rating scale from “completely disagree” to “totally agree”. The GSES-10 measures confidence in one’s own ability to handle stressful situations. The instrument is used internationally and has shown good internal reliability; in this study, the Swedish version of the GSES-10 will be used [61].The Self-Efficacy for Exercise (SEE) scale [62]. This instrument will be used to measure self-efficacy barriers to exercise in the study population. The SEE-S is a 13-item instrument that focuses on self-efficacy expectations related to the ability to continue exercising in the face of barriers to exercise. There is evidence for reliability and validity of the SEE scale [62].Insomnia Severity Index (ISI) scale [63]. This is a brief self-report instrument consisting of seven items measuring the person’s perception of insomnia. Each item is rated on a 0–4 scale and the total score ranges from 0 to 28. A higher score suggests more severe insomnia. The ISI scale has been reported to have good reliability and validity [63].

Cost estimates for the health economic evaluation:

Health care consumption and productivity loss (sick leave) will be estimated using data from administrative systems and/or medical records in health care. Costs will be estimated by multiplying frequencies by national Swedish tariffs and market prices. Total costs for each group will be aggregated over the trial period.Intervention cost will be estimated based on information provided by the persons responsible for the intervention.

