#### Health economic evaluation

A within-trial (3 months) and a long-term (1 year) cost–utility analysis will be performed from both health care and societal perspectives. The base case will consider health care costs and productivity loss. Gained QALYs will be used to measure effects. Cost-effectiveness ratios will be based on changes in QALYs and net costs of the intervention groups versus those in the control group. Results will be presented as an incremental cost-effectiveness ratio (ICER) expressed as (Ca – Cb)/(Ea – Eb). The uncertainty around the cost and effect estimates will be expressed in sensitivity analyses.

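### The QALY rule's EQ-5D-5L time points conflict with Table 3: it uses an unscheduled 3-week value and omits the scheduled 12-week value

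*Protocol article*

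**What the plan says.** Under Secondary outcome measures, time in each health state is multiplied "by the average utility weight associated with the period (using the trapezium rule), quality-adjusted life years (QALYs) will be derived". The measurement points for this are listed as "baseline – 3 weeks – 6 weeks – 9 weeks – 6 months – 12 months". The list has a 3-week point and no 12-week point.

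In Table 3 (Outcome measures), the row "Quality of life (QoL) assessed with the EQ-5D-5 L" has marks at visit 1, 6 weeks, 9 weeks, 12 weeks, 6 months and 12 months. Its 3-week cell is empty. The column for the last on-treatment visit is headed "12 weeks (end of the intervention").

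The Health economic evaluation section announces "A within-trial (3 months) and a long-term (1 year") cost–utility analysis. On the effect side it states: "Gained QALYs will be used to measure effects".

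The Data collection section gives the general calendar: "Data will be collected before the intervention, during the intervention at week 3, 6 and 9, and directly after the 12-week intervention". It does not say which instruments are used at which visit. It counts the 6- and 12-month follow-ups from the start of the intervention.

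**The concern.** The article fixes an exact computational rule for the effect measure of both cost–utility analyses, and the rule does not match the article's own measurement schedule. An analyst who follows the text will look for a week-3 utility that Table 3 does not plan, and will leave out the utility measured when the programme ends.

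Week 12 matters for two reasons. It is the closing point of the 3-month horizon. It is also the last measurement before controls are offered physiotherapy-supported training. The Discussion says that controls who start the physiotherapy-led intervention are not included in the long-term follow-up and count as internal dropouts. Their 6-month utility would therefore not be observed, and a line from week 9 to month 6 would have to end on an imputed value.

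At stake are the QALY gains, and through them the cost-effectiveness ratios. If the conflict is settled only after the data are seen, the choice of utility points becomes a post hoc choice that moves the ratio.

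**Working it through.** The article states no QALY figure, so there is none to reproduce. The check compares the two schedules and then works out what the difference does to the trapezium rule.

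**1. The two schedules**

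| Time | QALY list (Secondary outcome measures) | EQ-5D-5L row (Table 3) |
|---|---|---|
| Baseline / visit 1 | yes | yes |
| 3 weeks | yes | empty |
| 6 weeks | yes | yes |
| 9 weeks | yes | yes |
| 12 weeks | no | yes |
| 6 months | yes | yes |
| 12 months | yes | yes |

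The EQ-5D-5L row fills the same nine columns as the header. The SEE-S and ISI rows, marked at every visit, confirm the column order. The row is therefore not shifted.

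**2. Trapezium weights for the 1-year QALY**

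Take 6 and 12 months as weeks 26 and 52 from the start, as in Data collection. The weight of an inner point is (next time − previous time) / (2 × 52).

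- Week 12 on the Table 3 grid: (26 − 9)/104 = 0.1635. On the written list: 0.
- Week 9: (12 − 6)/104 = 0.0577 on the Table 3 grid, (26 − 6)/104 = 0.1923 on the written list.
- Month 6: (52 − 12)/104 = 0.3846 on the Table 3 grid, (52 − 9)/104 = 0.4135 on the written list.

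The weight of week 12 passes to its neighbours: 0.1346 to week 9 and 0.0288 to month 6.

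**3. The 3-month QALY**

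On the Table 3 grid, weeks 0, 6, 9 and 12 have weights 6/104, 9/104, 6/104 and 3/104. These sum to 24/104 = 12/52 year, so the horizon is fully covered. On the written list the last utility inside the horizon is at week 9 and the next is at month 6, 17 weeks later. The last 3 of 12 weeks (25%) must be interpolated.

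**4. Size of the error**

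Let d be the true between-group gain at week 12 minus the value on the straight line from week 9 to month 6. Omitting week 12 changes the 1-year gain by −(17/2) × d = −8.5d utility-weeks. It changes the interpolated 3-month gain by −(3/2) × d = −1.5d. The sign depends only on whether the week-12 gain lies above or below that line. Whether a week-3 value exists does not alter this when the early rise is linear.

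*Path A (assumed):* gain rising linearly to 0.06 at week 12, then 0.02 at month 6 and 0 at month 12.

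- 1 year with week 12, in utility-weeks: 0.09 + 0.1125 + 0.1575 + 0.56 + 0.26 = 1.18; 1.18/52 = 0.0227 QALY.
- 1 year without week 12: 0.09 + 0.1125 + 17 × (0.045 + 0.02)/2 + 0.26 = 1.015; 1.015/52 = 0.0195 QALY, or −14%.
- 3 months with week 12: 0.36/52 = 0.00692 QALY.
- 3 months interpolated: week-12 value 0.045 + (3/17)(0.02 − 0.045) = 0.0406, giving 0.00636 QALY, or −8%.

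*Range around path A:* keep a linear rise to a peak at week 12, with 0%, 50% or 100% of it remaining at month 6, and 0 at month 12 (or the peak held, in the 100% case). The 1-year gain is then 25%, 11% or 4% too low, and the interpolated 3-month gain 10%, 7% or 5% too low. These percentages do not depend on the height of the peak.

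*Path B (assumed):* gain linear from week 9 to month 6. Then d = 0 and there is no error.

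*Path C (assumed):* gain rising to 0.03 at week 6, flat to week 12, then 0.06 at month 6 and 0 at month 12. With week 12: 0.09 + 0.09 + 0.09 + 0.63 + 0.78 = 1.680 utility-weeks. Without it: 0.09 + 0.09 + 0.765 + 0.78 = 1.725, or 2.7% too high.

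**The case against.** The strongest reply is that this is a slip in a parenthesis. Table 3 schedules the EQ-5D-5L at 12 weeks and Data collection confirms a visit directly after the programme. An analyst closing a 3-month analysis would naturally use that value. This largely stands as an account of how the conflict arose. It does not remove the conflict, because the list is the only stated rule for the QALY and nothing else in the article overrides it.

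Three stronger readings are tempting and are not supported.

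- A reader might infer that the 3-month analysis has no utility at its end point, or cannot be computed. The utility is planned in Table 3, and even the listed points allow an interpolated result.
- A reader might infer a large loss because the calculation would stop at week 9. No section proposes that.
- A reader might infer that the QALY gain will be understated because the effect is greatest when the programme ends. The article gives no utility values and no statement about when the utility gain peaks. Path A builds the understatement in by placing the peak at the omitted visit. Paths B and C give none or the reverse.

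It is also fair to say that Table 3 may be the passage in error on week 3. Week 3 is a general collection point, other questionnaires are given then, and Table 3 has oddities elsewhere, such as a CGI-S mark under the column for who completes the form. The article does not settle which is right for week 3. For week 12 the case is clearer, since the 3-month horizon needs that value and the table provides it.

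**Conclusion.** The inconsistency is real and is wrong as written. The QALY rule uses an unscheduled week-3 utility and gives zero weight to the scheduled week-12 utility, which should carry about 0.16 of the 1-year QALY and should close the 3-month one. These weights follow from the schedule alone, with 6 and 12 months counted from the start of the intervention. The Abstract can be read as counting them from the end, which would change the weights but not the conflict.

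The effect on the results cannot be stated as a known bias. The figures of about 14% (1 year) and 8% (3 months, interpolated) hold only for the assumed path that peaks at week 12. Other assumed paths give no error or one in the other direction.

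Severity is moderate. Cost-effectiveness is a secondary aim, the primary outcome and sample size are untouched, and no planned data are lost.

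**What to change.** Reconcile the QALY sentence under Secondary outcome measures with Table 3:

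- Add 12 weeks to the list of utility points.
- State that the 3-month analysis closes at week 12 and the 1-year analysis at month 12.
- For week 3, either remove it from the list or, if the EQ-5D-5L is in fact given then, mark it in Table 3 and keep it in the list.

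This costs one line of text and possibly one table cell. It needs no new data and should be done before the economic data are analysed.

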**Type of intervention: MEP** – a structured physiotherapy-led exercise programme; or **MEP-C** – MEP together with an occupational therapist-led, person-centered cognitive intervention.**Dose, MEP**: Physical exercise for 45 min, three times a week for 12 weeks. **Dose, MEP-C:** Occupational therapy for 60 min approximately six times (every second week) during the 12-week period depending on participant’s goals related to the intervention; and physical exercise for 45 min, three times a week for 12 weeks.**Dose, MEP**: Physical exercise for 45 min, three times a week for 12 weeks. **Components of physical exercises, MEP and MEP-C**: All exercise sessions will have the same structure and consist of endurance, strength and flexibility training. Desired heart rate (HR) range will be 60–90% of maximum HR. In order to track HR during all sessions, both in the clinic and at home, the participants will have a Polar Heart Rate Monitor, model H10 (Polar Electro Oy, Kempele, Finland), connected to their mobile phone. Each exercise session will start with 5–10 minutes’ **warm-up** on an ergometer or using body movements. Next will be **endurance exercises** in three to five intervals of 1 min work and 1 min active rest between each interval. The **strength training exercises** will consist of five different exercises with 1-minute intervals between exercises, in three rounds. These strength exercises may vary depending on the location, indoors or outdoors. However, they will always include one exercise mainly for leg strength, for example squats or lunges; one exercise for arms and shoulders, for example shoulder press with barbell or bench press; one core exercise, for example crunches or the plank; and one balance challenge, for example standing on one leg. The participants will be encouraged to do as many repetitions as possible in 1 min and therefore the load of the exercise can be altered depending on the number of repetitions the participant can manage. In the cool-down, in the warm-up and during stretching the participant will be encouraged to sense the feeling of the body and their overall feeling.**Components of the cognitive intervention of the MEP-C**: As previously mentioned, the cognitive intervention will be conducted by an occupational therapist on approximately six occasions during the 12-week period. Based on self-prioritized goals concerning structure, planning and organization in everyday life, a treatment plan for cognitive skills training will be drawn up. This will form the basis of the treatment. (Examples of such goals are: to arrive on time for training, or to create the space for physical activity in one’s everyday life through improved time management.)**Sequences**: The training sessions will take place either in the training facilities at the outpatient clinic or outdoors in a nearby park. Each session will follow a specific structure.**Modifications**: Alternative exercises will be suggested by the instructors when needed. Participants will be allowed to perform to the best of their ability, with encouragement from the physiotherapists to use maximum effort.**Selection of instructors**: The instructors for the physical exercise sessions will be licensed physiotherapists at the Unit for Psychiatric Physiotherapy, Region Örebro County, who are experienced in working with persons with ADHD. The instructors for the cognitive intervention will be occupational therapists with experience of both working with persons with ADHD and using the Canadian Occupational Performance Measure (COPM) as person-centred tool [33, 34].**Home practice**: In addition to the physiotherapist-led group, the participants will be expected to exercise individually once a week, to the extent needed to reach 150 minutes’ exercise per week. Participants receiving cognitive skills training will be given home assignments, primarily to implement compensatory cognitive strategies in daily life.**Fidelity**: Training adherence will be noted by the treating physiotherapist and occupational therapist. Group adherence to physical activity will be calculated as the number of patients attending 50% of the sessions. To maintain physical exercise for at least 150 min per week, the HR monitor connected to the participants’ mobile phone will gather the time in an HR zone of > 60%. Attendance rate over the intervention period will be calculated as a mean of the individual percentage.**Control group**: Participants randomized to the control group will continue with their TAU. This will include any ongoing pharmacological and/or non-pharmacological treatment that does not include physical exercise or cognitive skills training during the 12-week period. After the 12-week data collection, the participants will be offered physiotherapy-supported training outside the framework of the study.

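### The societal cost-utility analysis names sick leave as its only productivity loss, so work time lost to attending START sessions could go uncounted

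*Protocol article*

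**What the plan says.** The Health economic evaluation section of the protocol article states: "A within-trial (3 months) and a long-term (1 year) cost–utility analysis will be performed from both health care and societal perspectives". It continues: "The base case will consider health care costs and productivity loss". The result is an ICER, the cost difference (Ca – Cb) divided by the QALY difference (Ea – Eb), and uncertainty is to be handled in sensitivity analyses that are not specified.

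The cost items are at the end of Secondary outcome measures, under the cost estimates for the health economic evaluation. On productivity: "Health care consumption and productivity loss (sick leave) will be estimated using data from administrative systems and/or medical records in health care". On the programme itself: "Intervention cost will be estimated based on information provided by the persons responsible for the intervention". The components of that intervention cost are not listed.

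The section on the START intervention programme sets the dose. Both START arms have three 45-minute exercise sessions a week for 12 weeks. MEP-C adds: "Occupational therapy for 60 min approximately six times (every second week) during the 12-week period". Controls receive neither exercise nor cognitive skills training in that period. On attendance, the Fidelity paragraph says: "Training adherence will be noted by the treating physiotherapist and occupational therapist".

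**The concern.** A societal perspective is meant to count productive time that is lost, whatever the reason. The article narrows productivity loss to sick leave and names the sources from which it will be read. A participant who leaves work for an exercise or occupational therapy session is not on sick leave, and neither source would be expected to show that absence as sick leave.

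The possible omission is not shared equally between arms. By design, only MEP and MEP-C participants have these sessions, and MEP-C participants have more of them. Taken alone, leaving this time out can only lower Ca – Cb for START against TAU. QALY differences in a trial of this length may be small, and a small denominator lets modest uncounted costs move the ratio noticeably. Cost-effectiveness is a declared aim of the trial, so the societal label should match what is counted.

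**Working it through.** The plan gives no figure of its own for participant time, so there is none to reproduce. The inputs come from the protocol article.

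- Exercise, both START arms: 45 min, 3 times a week, 12 weeks (Intervention section, dose). Table 1 agrees: 6 + 6 + 23 + 10 = 45 min.
- Occupational therapy, MEP-C only: 60 min, about 6 times (same section).
- TAU: no such sessions during the 12 weeks (same section, control group).
- Minimum participation: 50% (Discussion).
- Not given: time of day of the sessions, share of participants in work, value of an hour, expected QALY gain.

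**Step 1, scheduled hours (h) at full attendance.**
- MEP: 45 × 3 × 12 / 60 = 27 h.
- MEP-C: 27 + 6 × 60 / 60 = 33 h (approximate, because the number of occupational therapy sessions is).
- TAU: 0 h.

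At 50% attendance these become 13.5 h and 16.5 h. Home exercise to reach 150 min a week would add 150 – 3 × 45 = 15 min a week, or 3 h over 12 weeks. It is done individually and is left out below. Travel time is not stated.

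**Step 2, uncounted work hours.** Let f be the share of session time that displaces paid work. The documents do not give f, so the whole range is shown. Uncounted hours = h × f.

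| f (assumed) | MEP | MEP-C |
|---|---|---|
| 0 | 0 h | 0 h |
| 0.25 | 6.75 h | 8.25 h |
| 0.5 | 13.5 h | 16.5 h |
| 1 | 27 h | 33 h |

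**Step 3, effect on the ICER, for illustration only.** With w the value of one hour, Ca – Cb is understated by h × f × w, and the ICER by h × f × w / (Ea – Eb) if the QALY gain is positive. QALY gains of 0.01, 0.02 and 0.04 are assumed. In units of w per QALY:
- f = 0: no shift in either arm.
- 75% attendance and f = 0.5: MEP 27 × 0.75 × 0.5 = 10.1 h, giving about 1,010, 510 and 250. MEP-C 33 × 0.75 × 0.5 = 12.4 h, giving about 1,240, 620 and 310.
- Full attendance and f = 1: MEP 27 / 0.01 = 2,700, then 1,350 and 675. MEP-C 33 / 0.01 = 3,300, then 1,650 and 825.

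**Step 4, the two horizons.** All led sessions fall within the first 12 weeks, so the 3-month analysis carries the full amount. The difference between arms also remains at 1 year: according to the Discussion, controls who start the physiotherapy-led intervention after week 12 are left out of the long-term follow-up, so their session time does not offset it.

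**The case against.** The strongest reply is that the article may simply not spell this out. Intervention cost is a separate line without listed components. The staff who would supply that information also note attendance, so participant hours could be part of it, and a full cost inventory is commonly left to a document not shown here. This stands in part: nothing excludes participant time. But the definition of productivity loss as sick leave, and its source, are stated choices rather than missing detail, and information from those running the programme most naturally means delivery resources.

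A second reply is that the loss may be nil. Sessions may fall outside working hours, missed sessions can be made up on another day or at home, and the Background describes difficulty in finding and keeping employment. This stands fully, and is why the range starts at 0 h.

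A third is that the planned sensitivity analyses could already cover the point. They could, but none is named, so the remaining request is to name this one.

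A reader might go further and infer that the societal ICER is tilted towards START. The documents do not support that. Counting only sick leave also misses better performance at work or gains in employment, which START might produce, and missing those would work against START. Nor is it right to say that productivity comes from health care records alone: the article allows administrative systems and/or medical records.

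**Conclusion.** The point holds in a limited form. The stated productivity measure is narrower than the societal perspective it serves, and it would not capture work time lost to attending START. The resulting understatement of START's incremental societal cost lies between 0 h and 27 h per participant in MEP, and between 0 h and about 33 h in MEP-C. The upper ends assume full attendance, every session displacing paid work, and participant time not already included in the intervention cost. The lower end applies if no session displaces paid work.

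The net direction of any bias in the societal ICER is not established. The ICER shifts in the working rest on assumed attendance, displacement and QALY gains, and they do not show that a conclusion would change. The health care perspective and the clinical outcomes are unaffected. This is an inexpensive improvement to a secondary aim.

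**What to change.** In the cost estimates paragraph and in Health economic evaluation, add a participant-time cost to the sensitivity analyses of the societal perspective:

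- Cost per participant = attended sessions (from the attendance notes) × session length (45 min for exercise, 60 min for occupational therapy) × a stated unit value of time.
- Report the societal ICER with 0% and with 100% of that time valued as lost work.
- State whether the intervention cost already contains participant time, so that it is not counted twice.

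If this is not wanted, label the second perspective 'health care plus recorded sick leave' and limit the conclusion to that.

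The cost is a change of wording in the economic analysis. Attendance is already noted and session lengths are fixed, so no data collection is added. The downsides are that a unit value of time has to be assumed, that attendance notes cannot show whether a session displaced work (so the 0% to 100% range cannot be narrowed from them), and that START's societal ICER may look less favourable at the upper end.
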